#### Tertiary outcomes and other measures

Alcohol use quantity and frequency as well as heavy episodic drinking was measured by *NIAAA’s* Alcohol Use Disorder and Associated Disabilities Interview Schedule-5 (AUDADIS-5) [64].Self and descriptive peer drinking norms as measured by the *Daily Drinking Questionnaire* [65]. Participants report how much alcohol they consume and how much alcohol they believe their peers consume during an average week over the past 3 weeks. Drinks per week are summed.Alcohol expectancies for aggression, sexual affect, sexual drive, and vulnerability to sexual coercion as measured by the *Alcohol Expectancies Regarding Sex, Aggression, and Sexual Vulnerability Questionnaire* [66]. Each item is rated on a 1 (not at all) to 5 (very much) scale. Scores are obtained by summing items on each subscale (aggression, sexual affect, sexual drive, and vulnerability) and dividing by the number of items on that scale. Higher means scores on each subscale reflect higher alcohol expectancies.Sexual violence perpetration in dating relationships as measured by the 7-item sexual coercion subscale of the *Revised Conflict Tactics Scale* [67]. Participants indicate the number of times that they perpetrated on a 7-point scale ranging from 0 (never) to 6 (more than 20 times). A frequency score is calculated by adding the midpoints of responses for each item, with higher scores reflecting greater sexual violence perpetration in dating relationships in the past year.Rape empathy as measured by the *Rape Empathy Scale* [68], which is comprised of 18-items that assess rape-victim empathy and 18-items that assess rape-perpetrator empathy on a 1 (strongly disagree) to 5 (strongly agree) scale. A mean score is computed for each subscale, with higher scores reflecting greater empathy.Peer disapproval for sexual aggression as measured by the 3-item *Differential Reinforcement Scale* [69]. Participants rate their level of agreement for each statement on a 1 (very approving) to 5 (very disapproving) scale, with greater mean scores indicating greater disapproval for sexual aggression.Peer network density as measured by the *Peer Density Network scale* [70]. Participants are asked to list five male peers with whom they most often associated in high school as well as the strength of each relationship between pairs on a 0 (never met) to 100 (extremely close friends) scale. Network density is calculated by averaging relationship strength across each of these peer relationships.

#### Participant timeline {13}

##### Sample size {14}

Sample size requirements were determined via a Monte Carlo simulation study based on Aim 2 analysis strategy, which will require a larger sample than Aim 1 analyses. The primary outcome for Aim 2 will be intervention proportion: the number of times each participant engaged in prosocial bystander behavior divided by the number of sexist or violent situations they encountered during a given assessment period. Sample size is therefore based on the number per treatment group needed to detect clinically meaningful effects on intervention proportion. Calculations were based on 80% power, level of significance of .05, and two-tailed statistical tests. Clinically meaningful treatment efficacy was based on previous research [23, 71] and was defined as having between a small and medium effect size between group intervention proportions (Cohen’s *h* ≥ .30). In this RCT, this effect size translated into a 15% point difference between groups, at a minimum, and could potentially translate to a clinically significant increase in bystander intervention for those who receive *RealConsent2.0*. Assuming control participants intervene in approximately 50% of all sexist or violent *non-alcohol* situations they encounter, those who receive RealConsent1.0 will intervene in 65% of those non-alcohol-related situations; those who receive RealConsent2.0 will also intervene in 65% of non-alcohol-related situations. For *alcohol-related* situations, we expect those in control and in RealConsent1.0 to intervene approximately 30% of the time whereas for RealConsent2.0, we expect 45% of the time they will intervene. Based on these proportion differences, a total of 484 participants are needed ~161 in each intervention group). We expect between 20% attrition based on previous work. To achieve adequate power, we estimated a needed sample size of at least 605 to maintain complete data for 484 participants for the per protocol analysis. Additionally, this sample size allows us to detect small differences (7%) in intervention rates within the VR paradigm as a function of intervention and beverage conditions, as well as their interactions.

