## Objectives {7}

The overarching goal of this project is to evaluate the efficacy of *RealConsent2.0*, which includes new program segments for promoting prosocial bystander behavior among intoxicated men. This aim is grounded in the evidence-based premise [28, 43, 44] that integrating alcohol-specific content within the context of *RealConsent1.0* (i.e., “*RealConsent2.0*”) will enhance prosocial bystander behavior among intoxicated bystanders. As such, we sought to achieve this goal by testing two related research questions: (1) Does *RealConsent2.0* facilitate more prosocial bystander intervention (assessed within a virtual environment) among intoxicated men relative to two comparison conditions (i.e., *RealConsent1.0* and *Taking Charge*)? and (2) Does *RealConsent2.0* facilitate more prosocial bystander intervention (assessed at 6- and 12-month follow-up) involving alcohol-related events relative to the two comparison conditions?

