## Statistical methods

### Statistical methods for primary and secondary outcomes {20a}

Data collected within the virtual environment will be structured as the proportional count of intervention behaviors relative to the number of opportunities to intervene. We will test all Aim 1 hypotheses using generalized linear models based on either Poisson or negative binomial distributions, depending on if a given model is overdispersed. These are appropriate statistical models to use in this case because we expect this proportional count outcome to be positively skewed based on pilot research. We will analyze *Aim 2* RCT data with an intent-to-treat and per protocol analyses. An intent-to-treat analysis includes all participants who were randomized, regardless of compliance, withdrawal, and anything that happens after randomization. An advantage is that it is an analysis based on original randomization; however, effect estimation may be conservative and misleading with increasing attrition. A per protocol analysis considers only participants who fully complied and completed the study. Per protocol is less conservative and may reflect true treatment differences for those with full compliance. Including an intent-to-treat and per protocol analysis will provide a more complete understanding of treatment effects. Outcomes, including prosocial bystander behaviors, will be modeled using a generalized linear mixed model. This is an appropriate statistical model to use with repeated measures data collected over time [73]. Random effects for subject will be included to account for the multiple measurements taken at baseline and 6- and 12-month follow-up on each subject. Intervention condition will be dummy coded, with variables representing both the *RealConsent1.0* and *RealConsent2.0* conditions, with *Taking Charge* as reference group. Planned contrasts will be conducted between *RealConsent1.0* and *RealConsent2.0* groups.

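### The Aim 2 primary outcome is defined over all situations, but the research question and the sample size are alcohol-specific; the stated 80% power for RealConsent2.0 v RealConsent1.0 holds only on the alcohol-specific reading

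*Protocol article*

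**What the plan says.** Sample size {14} in the Protocol article names one Aim 2 primary outcome, the intervention proportion: "the number of times each participant engaged in prosocial bystander behavior divided by the number of sexist or violent situations they encountered" in an assessment period. It says that the sample size rests on effects on this proportion. "Calculations were based on 80% power, level of significance of .05, and two-tailed statistical tests". The target effect is Cohen's h of at least 0.30, and "this effect size translated into a 15% point difference between groups, at a minimum".

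The expected rates that follow are set by context.

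- Non-alcohol situations: "Assuming control participants intervene in approximately 50% of all sexist or violent" situations of this kind. RealConsent1.0 is put at 65%, and "those who receive RealConsent2.0 will also intervene in 65% of non-alcohol-related situations".
- Situations that involve alcohol: "we expect those in control and in RealConsent1.0 to intervene approximately 30% of the time whereas for RealConsent2.0, we expect 45% of the time".

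From these the section derives 484 completers (about 161 per programme) and, with 20% attrition, 605 randomised.

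Objectives {7} frames research question 2 as bystander intervention at 6 and 12 months "involving alcohol-related events relative to the two comparison conditions".

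Statistical methods {20a} says: "Outcomes, including prosocial bystander behaviors, will be modeled using a generalized linear mixed model". It gives programme indicators with Taking Charge as reference, a random subject effect, and a planned contrast of RealConsent1.0 with RealConsent2.0. It mentions no alcohol context.

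**The concern.** The outcome definition covers every situation a man encountered, while the question it serves and the rates used for sizing are specific to alcohol-related situations. This matters most for RealConsent2.0 v RealConsent1.0, the contrast that shows whether the new alcohol content adds anything. The plan expects no difference between these two programmes outside alcohol contexts. If contexts are pooled, a real 15-point gain in alcohol-related situations is averaged with situations where none is expected. The contrast then loses power, and a positive pooled result would not by itself answer the question about alcohol-related events. If the definition stays ambiguous, the choice between the two outcomes could also be made after the data are seen.

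**Working it through.** **Inputs (Sample size {14}).** Two-sided 0.05, 80% power, 161 completers per programme. Rates for Taking Charge / RealConsent1.0 / RealConsent2.0 are 30 / 30 / 45% in alcohol-related situations and 50 / 65 / 65% in non-alcohol situations. The share s of situations that involve alcohol is not given. The nearest figure is in Background {6a}, where 50–77% of sexual violence incidents involve alcohol. That is only a proxy for the situations men report here, so s = 0.50 and s = 0.77 are used as assumptions.

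**Step 1: the plan's own figure.** With h = 2·arcsin√p2 − 2·arcsin√p1 and n = 2(1.96 + 0.8416)²/h² per group:

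- 30% v 45%: h = 0.311, n = 162 per group, 486 in total. The two usual formulas for a difference in proportions give 160 (unpooled variance) and 163 (pooled variance), so 480 and 489. Power at 161 is 79.7%.
- 50% v 65%: h = 0.305, n = 170 per group, 510 in total. Power at 161 is 78.0%.
- Attrition: 484/0.80 = 605.

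The alcohol-related pair reproduces 484; the non-alcohol pair does not quite. Both pairs are specific to a context, and neither is a rate over all situations. The article says that N came from a Monte Carlo simulation. Its settings are not given, so that run cannot be repeated.

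**Step 2: the pooled outcome.** The pooled rate is s × alcohol rate + (1 − s) × non-alcohol rate. For RealConsent2.0 minus RealConsent1.0 the 65% terms cancel, so the difference is 0.15 × s.

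- s = 0.50: 47.5% v 55.0%, difference 7.5 points, h = 0.15
- s = 0.77: 38.05% v 49.6%, difference 11.55 points, h = 0.233

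**Step 3: power at 161 per group, RealConsent2.0 v RealConsent1.0.** Two approaches bracket the answer.

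(a) One binary observation per man, the formula that reproduces 484: power = Φ(h·√(161/2) − 1.96).

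(b) Take the plan's 80% for the alcohol-only contrast as given (standardised effect 1.96 + 0.84 = 2.80) and credit the pooled proportion with the precision gained from more situations per man. With no within-man correlation, the best case, power = Φ(2.80·√s − 1.96). With complete correlation, power = Φ(2.80·s − 1.96).

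| Assumed s | (a) one unit per man | (b) complete correlation | (b) no correlation |
|---|---|---|---|
| 0.50 | 27% | 29% | 51% |
| 0.77 | 55% | 58% | 69% |
| 1.00 | 80% | 80% | 80% |

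**Step 4: the other comparison in research question 2.** RealConsent2.0 v Taking Charge at s = 0.50 is 55% v (0.5 × 30% + 0.5 × 50%) = 40%. The difference is still 15 points, and power is 77%.

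**Step 5: can the alcohol-specific proportion be built?** Under Outcomes {12}, the Bystander Behavior Scale counts each behaviour from 1 to 3 or more times, both when the man intervened and when he had the opportunity but did not. Whether he or others were drinking is asked only about the most recent occasion. An alcohol-specific proportion over all counted occasions cannot be fully formed from these items, so a scoring rule is needed.

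**The case against.** The strongest reply is that pooling is never stated. The Abstract, Objectives {7} and the choice of comparators {6b} all distinguish alcohol from non-alcohol behaviour. Sample size {14} itself applies the proportion within each context straight after defining it. On this view the definition is a general formula used separately by context, and power is about 80%. This stands to the extent that the authors probably intended a context-specific analysis. It does not remove the conflict, because the only stated definition of the primary outcome has all situations in its denominator and the article says that N is based on that outcome.

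A reader might infer from Statistical methods {20a} that a pooled test is definitely planned, because the model names no alcohol-context term. The article does not support that. It is a condensed account that leaves model details to documents not shown, and its silence on one term is weak evidence. The point rests on the outcome definition.

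A reader might also infer that the trial has only 27% to 51% power. That too goes beyond the document. The range requires both a pooled analysis and an assumed 50% share. The 27% end treats each man as one binary observation. Several situations per man could raise pooled power, but would raise alcohol-only power as well, which is why approach (b) ties the calculation to the plan's own 80%.

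Finally, the match of 484 to the alcohol-related rates is narrow (79.7% against 78.0% power at 161 for the non-alcohol rates). It supports the statement that N came from context-specific rates better than the statement that the alcohol contrast alone drove it.

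**Conclusion.** The point holds as an internal contradiction about the Aim 2 primary outcome. The definition covers all situations; research question 2 and the sizing inputs are context-specific. If the alcohol-related proportion is analysed, power for RealConsent2.0 v RealConsent1.0 is about 80% and the sample size stands. If the pooled proportion is analysed as defined, the stated 80% does not hold for that contrast at any alcohol share between 50% and 77%.

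These figures rest on the plan's own rates, on 161 completers per group, on the assumed share, and on the plan's 80% for the alcohol-only contrast being right. The loss is confined to contrasts that pooling dilutes; RealConsent2.0 v Taking Charge largely escapes it. The contradiction should be resolved before analysis, because it bears on the contrast that isolates the new content.

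**What to change.** Reconcile Objectives {7}, Sample size {14} and Statistical methods {20a}. State that the Aim 2 primary outcome is the intervention proportion in alcohol-related situations, with RealConsent2.0 v RealConsent1.0 and v Taking Charge as the primary contrasts, and that the non-alcohol proportion is a separate outcome. Alternatively, model both contexts with a programme-by-alcohol-context term and take the primary contrasts within the alcohol context.

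State the scoring rule as well, including whether drinking by the participant, by others, or by either makes an occasion alcohol-related. One workable rule builds the proportion from the most recent occasion of each behaviour.

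The cost is revised wording and, on the second option, one more model term. The small downside of the suggested scoring rule is that it uses only part of the counted occasions. No extra participants or data collection are needed.

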#### Recruitment {15}

Participants are recruited from metropolitan areas of Atlanta, Georgia, and Lincoln, Nebraska, using in-person and online recruitment strategies. In-person methods include fliers posted throughout the community (e.g., grocery stores, coffee shops, university campuses), direct recruitment (research staff handing out fliers at public venues), and snowball sampling (at the end of the lab session, participants are given a flier and encouraged to give it to someone who may be interested). Online methods include social media advertisements (e.g., Instagram, Facebook, TikTok, Twitter), advertisements on other websites (e.g., Craigslist), and university email listservs.

Both sites meet monthly to discuss the number of participants enrolled in the past month and set goals for the number of participants to be enrolled in the upcoming month. Each site meets weekly to discuss recruitment in relation to that month’s enrollment goal. Each site makes independent decisions to adjust recruitment accordingly by posting new community fliers, increasing the social media ad budget, increasing the number of participants emailed through university listservs, and/or employing other approved recruitment strategies that are not currently being used at that site. The project coordinators from each site meet bi-weekly to discuss current enrollment numbers and recruitment strategies utilized at each site.

A practical aspect of our study was that it was funded in September of 2019 and was substantially affected by the COVID-19 pandemic. In 2020 and 2021, many restaurants and bars were still closed or were operating at limited capacity with local mask mandates. As this study involves assessing alcohol consumption specifically within contexts involving groups of people socializing and drinking, we delayed the start of recruitment to ensure our results would be valid. Also, a significant part of our protocol involves in-person assessments where participants are scheduled to come into our labs located on each participating campus for the alcohol administration and the VR assessment. Thus, even with academic campuses opening up, we surmised that recruitment would be difficult given that participants would need to feel safe coming into our building, interacting with people, and taking off their mask to consume alcohol. Once restrictions were lifted and more restaurants and bars opened up in early 2022, we made the decision to begin recruitment. At first, recruitment efforts were slow; however, since January 2023, we have seen an increase in recruitment and have set an anticipated end date for recruitment of our baseline sample.

## Assignment of interventions: allocation

### Sequence generation {16a}

A separate allocation sequence was created for each site using an automated *stratified block randomization* program implemented through SAS. Participants are stratified by drinking level, resulting in two strata: heavy episodic drinkers (HED) and non-HED. For each stratum, a separate block randomization sequence was used to ensure that equal numbers of men are assigned across the six groups that represent treatment condition (*RealConsent1.0, RealConsent2.0, or Taking Charge)* by beverage condition (Alcohol or Placebo): *(1) RealConsent2.0*/alcohol, (2) *RealConsent2.0*/placebo, (3) *RealConsent1.0*/alcohol, (4) *RealConsent1.0*/placebo, (5) *Taking Charge*/alcohol, or (6) *Taking Charge*/placebo.

### Concealment mechanism {16b}

The prepopulated allocation spreadsheets are stored on a secured, password protected Dropbox folder for each site. Personnel involved in outcome assessment {i.e., the BSAVE coders and study statistician) do not have access to these spreadsheets.

### Implementation {16c}

The allocation sequence was generated by the project statistician and stored in the form of two separate prepopulated randomization spreadsheets, one for each site. Each spreadsheet contains two tabs, one for participants who meet the criterion for heavy episodic drinking and one for participants who do not. Once a new participant completes the Baseline Survey and passes the required data validity checks, the project coordinator checks responses to determine whether or not the participant meets the criterion for heavy episodic drinking. The project coordinator then selects the appropriate tab in the randomization spreadsheet and assigns the next available condition to the participant. The participant’s condition is then recorded on study tracking spreadsheets, so that research staff who are responsible for contacting participants and running study sessions know to which intervention and beverage condition the participant is assigned.

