## Trial design {8}

This trial is a 2 × 3 factorial, double-blind (i.e., participants and statistician), multisite, superiority randomized controlled trial with six parallel groups (see Fig. 1). The two independent variables are the web-based health promotion intervention (*RealConsent1.0*, *RealConsent2.0*, or *Taking Charge*) and beverage condition (Alcohol or Placebo). Eligible participants (40% of whom will be heavy-episodic drinkers) who provide informed consent will be randomized to one of six conditions using stratified, block randomization with equal allocation across groups. The primary study outcome is bystander decision-making and will be assessed via observable behaviors within a VR environment and via self-report within an online survey administered at baseline and 6- and 12-month post-intervention. This trial will include detailed, written instructions to achieve uniformity of the performance procedures, including screening, retention efforts, and adherence to CONSORT guidelines.

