**Fig. 2 Fig2:**
[figure not shown]
SPIRIT diagram of trial schedule of enrolment, intervention, and assessments. Note: BSAVE (Bystanders in Sexual Assault Virtual Environments), BBS (Bystander Behavior Scale), BSABI (Barriers to Sexual Assault Bystander Intervention); OEIS (Outcome Expectancies for Intervening Scale); BES (Bystander Efficacy Scale); BAS (Bystander Attitudes Scale); SES-SF (Sexual Experience Survey Short Form); ROLBS (Reactions to Offensive Language & Behavior Scale); SEI (Self-Efficacy to Intervene Scale); DDQ (Daily Drinking Questionnaire); AESASVQ (Alcohol Expectancies Regarding Sex, Aggression, and Sexual Vulnerability Questionnaire); CTS (Revised Conflict Tactics Scale); RES (Rape Empathy Scale); DRS (Differential Reinforcement Scale)

Within each of the five at-risk scenarios depicted in the BSAVE, participants are prompted at two points (with a flashing microphone icon) to verbalize their response in that situation—thus providing ten opportunities to intervene in sexual risk situations. A team of research assistants will use audio recordings of participants’ open-ended responses to the risk scenes, as well as non-verbal behaviors captured by the VR system, to code intervention behaviors in response to each risk scenario. The most central code of interest will reflect the presence or absence of intervention attempts (0 = no, 1 = yes) in response to each of the two SV intervention opportunities within each of five risk scenes. An index measure will be created based on these responses that can range from 0 to 10 and will be used in data analyses.

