## Assignment of interventions: Blinding

### Who will be blinded {17a}

Participants are blinded to the main study hypotheses. They are informed that they will be randomized to view one of three different web-based health promotion programs and that each program covers topics related to young men’s physical and mental health and well-being as well as how to deal with stressful situations. In addition, the biostatistician and outcome assessors, who code the B-SAVE data, are blinded to intervention and beverage condition.

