### Data management {19}

Two forms of data are being collected during this trial. Survey data collected via Qualtrics survey platform and B-SAVE audio recordings. Following completion of each survey via Qualtrics, study staff examine data validity (i.e., “attention check” items) and completeness. Survey data are stored on Qualtrics servers, which are protected by high-end firewall systems. Data are encrypted using Transport Layer Security (TLS) encryption (also known as HTTPS) for all transmitted data that are downloaded onto password-protected computers by the study PIs. Final datasets will be password-protected. Data management procedures are performed by the study staff.

The second form of data are the audio recordings of B-SAVE responses. Audio files are recorded on computer that operates the B-SAVE. After each laboratory session, these files are uploaded to a password-protected folder on a secure server. B-SAVE recordings are then transcribed and any identifying information is removed. B-SAVE transcripts are then double coded by a team of highly trained coders to ensure reliability.

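### The statistician described as blinded is also, by title, the one who generated the allocation list; the B-SAVE coding source is stated two ways, and allocation and programme arm are open to more staff than necessary

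*Protocol article*

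**What the plan says.** All references are to the protocol article.

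**Statistician.** Trial design {8} describes the trial as "double-blind (i.e., participants and statistician". Who will be blinded {17a} adds that "the biostatistician and outcome assessors, who code the B-SAVE data, are blinded to intervention and beverage condition". Concealment mechanism {16b}, on the stored allocation lists, says that "the BSAVE coders and study statistician) do not have access to these spreadsheets". Implementation {16c} then says: "The allocation sequence was generated by the project statistician and stored in the form of two separate prepopulated randomization spreadsheets".

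**Coding source.** Outcomes {12}, in the text after Fig. 2, begins its account of scoring with "A team of research assistants will use audio recordings of" the participants' responses, and adds non-verbal behaviour logged by the VR system. Data management {19} says that recordings are transcribed and stripped of identifying information, and that "B-SAVE transcripts are then double coded by a team of highly trained coders to ensure reliability".

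**Coordinator.** Under Implementation {16c}, each site has one spreadsheet with a tab for heavy episodic drinkers and a tab for the others. The coordinator reads the baseline responses, decides which stratum applies, goes to that tab and gives the participant the next unused condition.

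**Session staff.** The same section says that the condition is copied to tracking sheets so that staff contacting participants and "running study sessions know to which intervention and beverage condition the participant is assigned".

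**The concern.** The B-SAVE index is a primary outcome. It is built from human yes/no judgements on speech recorded in a staff-run session. For such an outcome, protection against bias rests on three things: nobody can foresee or steer the allocation, the people around the participant do not act on the arm, and those who score and analyse do not know it. The article claims the third for coders and statistician.

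The claim about the statistician conflicts with the account of who made the list. The claim about the coders depends on which of two descriptions of their material is followed. The procedure for the first leaves the list readable by the person who classifies the participant. On the second the article makes no claim, but it gives the programme arm to staff who do not appear to need it in the laboratory.

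At stake are whether the double-blind label can be defended when results are reported, and whether a beverage or programme difference could be put down to expectation or to selective assignment.

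**Working it through.** No figure in the plan needs reproducing. The check sets the sections side by side.

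**1. Statistician**

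| Section | Title used | What is said |
|---|---|---|
| Trial design {8} | statistician | blinded; one of two parties behind the label |
| Who will be blinded {17a} | biostatistician | blinded to programme and beverage |
| Concealment mechanism {16b} | study statistician | cannot see the allocation spreadsheets |
| Implementation {16c} | project statistician | generated the sequence stored in those spreadsheets |

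The article nowhere says that these titles belong to different people. If they are one person, the last row conflicts with the other three. Generating a sequence is not the same as knowing a given participant's arm, but the step between is short. Each participant takes the next unused slot within site and stratum, so anyone who keeps the sequence and has site, stratum and order of entry can rebuild every assignment.

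**2. Coding source**

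Outcomes {12} names audio plus VR-logged behaviour; Data management {19} names transcripts. The difference matters for beverage only. Alcohol participants start the task at a BrAC of .08% (Alcohol administration), and a voice may carry signs of that which a transcript largely removes. Speech does not disclose the allocation record, and sounding intoxicated does not indicate which programme was viewed.

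**3. Allocation**

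There are 2 sites × 2 strata = 4 sequences, two of them in each site's spreadsheet. At each enrolment, two next conditions (one per tab) are therefore available to the coordinator before the stratum is recorded. Assume that the two sequences are independent and that each of the six groups is equally likely to come next:

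- chance that the two next conditions coincide = 6 × (1/6)² = 1/6, so they differ with probability 1 − 1/6 = 5/6;
- chance that the two programmes coincide = 3 × (1/3)² = 1/3, so they differ with probability 1 − 1/3 = 2/3.

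Thus a changed stratum decision would usually change the assignment. This shows that the stratum decision matters. It does not estimate how often a decision would be changed.

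**4. Session staff**

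The start rule differs by beverage (immediately after drinking for placebo, on reaching the target BrAC for alcohol), so staff must know the beverage. No laboratory step described in the article depends on the programme.

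**The case against.** **Statistician.** Three different titles are used, and they may be different people. The sequence came from an automated SAS program, the coordinator links people to slots, and the access statement may describe only the spreadsheets in use. Who runs the models is often left to a fuller document. This makes the conflict conditional but does not remove it: the article itself makes the blinding claim, and a retained copy of the sequence would be enough to defeat it.

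**Coders.** The two sections can be read as one pipeline, with audio as the source and transcripts as what is coded. A reader might infer that the audio sentence contradicts the coders' blinding. The documents do not support that: coders have no list, and audio is only a possible cue to the beverage. Nor does it readily reach the main Aim 1 question, which compares programmes among intoxicated men, where a correct guess of alcohol is the same in every arm. What stands is that the two descriptions should agree.

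**Session staff.** A reader might infer that their knowledge breaks the double-blind label. It does not: the label names participants and statistician, {17a} adds coders, and nobody claims that session staff are blinded. Staff who send programme access and reminders plausibly need the programme arm, and the task prompts participants with an on-screen icon. What stands is that this need does not extend to the laboratory session.

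**Coordinator.** The stratum is read from survey answers, so discretion may be small, and the text puts the stratum check before the choice of tab. A reader might also suppose that the coordinator clears the validity checks; Data collection {18a} and Data management {19} give these to study staff. The point about the open list stands without that.

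**Conclusion.** The point holds in four parts of different strength.

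- **Statistician:** a conflict on the face of the text if the titles denote one person. The article does not settle this, so it cannot be said that the analyst is in fact unblinded.
- **Coding source:** two sections disagree. Following the audio version would weaken the claimed blinding to beverage. That intoxication is audible at the target BrAC is an inference for which the document has no data.
- **Allocation:** as written, upcoming assignments can be known before the stratum is fixed. This is a concealment weakness and bears on both primary outcomes.
- **Session staff:** an avoidable performance-bias risk to the B-SAVE outcome, with no breach of any stated claim.

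The size of any resulting bias cannot be derived from the document, and no figure should be attached to it. The coding and session-staff parts do not touch the Bystander Behavior Scale, which participants complete themselves in an online survey. The text and procedures should be corrected because the exposure is avoidable at little cost, not because bias has been shown.

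**What to change.** 1. **Statistician.** State who generated the list and who analyses. Have the primary models run on masked group codes by someone who did not generate the list, or delete the claim of a blinded statistician in {8}, {16b} and {17a}. An existing team member can run the masked models, so no extra staff are needed.
2. **Coding source.** Align Outcomes {12} with Data management {19}: code from de-identified transcripts plus the VR log of non-verbal behaviour. The small cost is that coders lose tone of voice.
3. **Allocation.** Record and lock the drinking stratum before any condition can be seen, then reveal one assignment at a time instead of giving the coordinator the full prepopulated tabs.
4. **Session staff.** Give laboratory-session staff a tracking sheet that shows the beverage only, and keep the programme arm with those who send programme access and reminders.

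The cost is limited to edits to the article, the coding manual and the tracking sheets, and a change in how the list is released. For participants already enrolled, report which coding material was used and who had access to the list.
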